## Abstract

**Introduction:**

Mental well-being is associated with many mental health symptoms, including depression and health-related quality of life. Digital divide could impact mental health, particularly during the COVID-19 pandemic. Information and communication technology (ICT)-based tools and interventions could effectively provide social support. Intergenerational mentoring between college students and older adults could promote eHealth literacy and self-efficacy, and it is advocated to bridge the digital divide for older adults. However, the effectiveness of an intervention which employs ICT-based tools and intergenerational mentoring strategies (i.e. Digital Buddy) on mental well-being is unclear.

**Methods:**

This study will employ a multi-centre, cluster-randomized, two-parallel-group, noninferiority, controlled trial design with a 1:1 group allocation ratio. In the intervention group, a Digital Buddy (i.e. a young volunteer) is assigned to a group of older adults in a 1:10 ratio. A series of training sessions for a minimum of 23 h will be provided to the older adults by Digital Buddy, who will also follow through the intervention period with the older participants. The training contents include ICT and mental health care knowledge and skills. The whole intervention period will last for 6 months between 14 sessions. In the control group, participants will receive the usual care. The primary outcome measure is mental well-being. We aim to recruit 292 older participants. Generalized estimating equations (GEE) will be used to examine the effects of the intervention.

**Ethics and dissemination:**

This trial has been registered at ClinicalTrials.gov (NCT05553730) on 23 September 2022, https://clinicaltrials.gov/ct2/show/NCT05553730, and all items come from the World Health Organization Trial Registration Data Set. It has been approved by the Research Ethics Committee of Tung Wah College, Hong Kong (reference number: REC2022143). The findings will be disseminated in peer-reviewed journals and presented at international conferences relevant to the subject fields.

## Introduction

Mental well-being, as defined by WHO, is a state where people realize their abilities, can cope with the normal stress of life, can work productively, and can contribute to their community [1]. It is more than the absence of mental disorders or disabilities. The stress of life across the lifespan (e.g. the COVID-19 pandemic, organizational stress) is known to be associated with poor mental well-being [2, 3]. Mental well-being is associated with many health mental health symptoms, including depression and health-related quality of life [4, 5]. Under the influence of the prolonged COVID-19 pandemic and its related policies (e.g. quarantine, lockdown), older adults’ mental well-being is negatively affected [6]. A recent study in Hong Kong showed that older adults experienced a much higher level of depressive symptoms compared with the pre-pandemic period [7, 8].

Digital divide refers to inequalities of access to information and communication technologies (ICT), such as the ability to use computers, smartphones, or the internet, because of demographic differences (e.g. age, income, education) [9]. During the pandemic period, even in the developed world, difficulties in the utilization of digital healthcare among older adults continued to be observed [10]. Latest surveys in Hong Kong found that smartphone ownership and internet usage among those aged 65 or above have increased from 57.2% and 56.3% in 2018 to 68.1% and 65.9% by the second half of 2020. Yet, these figures are still far below those of younger age groups, which have capped at > 98% [11]. A study explicitly showed that the digital divide between older adults (age > 75 years) and their counterparts exist in terms of internet use for health information (OR = 0.37) [12]. Albeit the fact that mental well-being is known to be associated with classic health behaviours, such as physical activity and body-mind exercise [8, 13]; recent studies suggested that the digital divide could impact mental health, particularly during the COVID-19 pandemic [14].

Social support refers to the social resources available in the context of formal support groups and informal helping relationships [15]. Evidence suggests that social support is positively associated with mental well-being, particularly in vulnerable people [16, 17]. A longitudinal study showed that the mental well-being of older adults improved significantly after the gradual recovery of social support services during the relenting COVID-19 pandemic in the UK [18]. A systematic review showed that ICTs-based tools and interventions could effectively provide social support [19]. Therefore, enhancing social support through the provision of ICT-based tools and interventions could promote mental well-being.

Self-efficacy refers to an individual’s belief in their capacity that they can influence the results [20]. Evidence shows that self-efficacy is positively associated with mental well-being [21]. A study showed that a training programme is effective to enhance older adults’ self-efficacy and attitudes toward computers and the internet [22]. With well-planned instructions, the uptake and feasibility of ICT-based interventions are very high [23–25].

Intergenerational mentoring refers to the positive aspects of reverse mentoring without the hierarchical framework of mentor and mentee in that it focuses on the belief that everyone leads and everyone learns [26]. Intergenerational mentoring between college students and older adults could promote eHealth literacy and self-efficacy, and it is advocated to bridge the digital divide for older adults [27]. Evidence suggests that older adults could acquire new digital skills through explicit and on-explicit learning dynamics in their interaction with the young people in their families [28].

To summarize the evidence in the literature illustrated above, the digital divide in older adults may potentiate the detrimental effects of the COVID-19 pandemic on mental well-being and eventually on their health-related quality of life. A programme of intergenerational mentoring coupled with ICT training aiming at bridging the digital divide, providing better social support, and promoting self-efficacy may be a solution to promote the mental well-being and health-related quality of life of older adults. However, evidence of these hypothetical relationships is lacking in the literature. Therefore, this study aims to evaluate the effectiveness of a Digital Buddy programme on the mental well-being, depressive symptoms, health-related quality of life, self-efficacy, and social support of older adults. This study will yield knowledge about the effects of a new intervention modality to promote the mental well-being of older adults in places with the digital divide.

## Methods

This randomized controlled trial protocol reports the methods following the Standard Protocol Items: Recommendations for Interventional Trial (SPIRIT) 2013 guideline [29].

### Trial design

This study will employ a multi-centre, cluster-randomized, two-parallel-group, noninferiority, controlled trial design with a 1:1 group allocation ratio.

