#### Control group

Participants in the group will receive the usual care. The research team will not provide any form of support to the participants in this group.

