### Sample size

We adopt a prior power analysis using the GPower employing the statistical test of the mean difference between two different groups. We set the level of significance at 0.05, the power at 0.8, and the allocation ratio between the two groups at 1:1. To estimate the effects, we refer to a similar pilot trial examining the effect of an intergenerational mentoring programme [43]. The effect size (i.e. Cohen’s *d*) of the study of the intervention on the primary outcome (i.e. well-being) was 0.5. A sample size of 102 participants is needed. We adopt Hemming’s method to adjust the sample size required under individual randomization for cluster RCT with fixed and equal-sized number clusters [44]. Considering that we will collect data in 6 clusters and assuming that the intra-cluster correlation coefficient (ICC) is 0.01, the estimated total sample size is 244 (i.e. 122 per arm). We assume that the drop-out rate is approximately 20%. A total sample of 292 is estimated, with 146 participants in each arm.

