**Fig. 2 Fig2:**
[figure not shown]
Cluster randomization method

A waitlist control design will be adopted so that the participants randomized into the control group will be provided with a chance to receive the intervention after they have completed their untreated condition (i.e. receiving usual care for 6 months).

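### The trial is labelled noninferiority, but no margin is stated and its aim, comparator, sample size and planned test are those of a superiority trial

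*Protocol article*

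**What the plan says.** The Trial design section of the protocol article states: "This study will employ a multi-centre, cluster-randomized, two-parallel-group, noninferiority, controlled trial design with a 1:1 group allocation ratio". The Methods paragraph of the Abstract uses the same label. The word noninferiority appears nowhere else, and no margin is given.

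The other elements that define the hypothesis are these:

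- **Aim (end of the Introduction):** "this study aims to evaluate the effectiveness of a Digital Buddy programme on the mental well-being", followed by the secondary outcomes. The Discussion likewise speaks of promoting well-being.
- **Comparator (Control group):** usual care, with the statement "The research team will not provide any form of support to the participants in this group". Under Assignment of interventions, control participants are offered the programme "after they have completed their untreated condition (i.e. receiving usual care for 6 months".
- **Sample size:** "We adopt a prior power analysis using the GPower employing the statistical test of the mean difference between two different groups". It continues: "We set the level of significance at 0.05, the power at 0.8, and the allocation ratio between the two groups at 1:1". The effect entered is Cohen's d = 0.5, described as the effect of a similar mentoring programme on well-being in a pilot trial.
- **Statistical methods:** a GEE for each outcome with group, time and group × time, a significance level of 0.05, and intention to treat. The section mentions four hypotheses for five outcomes and writes out none of them.

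**The concern.** A noninferiority trial asks whether a new treatment is worse than a comparator by no more than a pre-set amount. The question makes sense when the comparator has a benefit worth preserving. Here the comparator is the absence of the programme. Showing that 23 hours of added training is not much worse than adding nothing would not answer the question posed in the Introduction.

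The declared framework decides what the primary result means. Under a superiority framework, a group × time estimate near zero is a failure to show benefit. Under a noninferiority label with no margin, the same estimate can be presented as success once a convenient margin has been chosen. A clear benefit would also be reported under a framework that does not fit it.

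**Working it through.** **1. Which hypothesis does the sample size carry?**

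Inputs from the Sample size section: d = 0.5, alpha 0.05 (sidedness not stated), power 0.80, allocation 1:1. The method is the two-sample t-test with the noncentral t distribution.

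| Test | Per arm | Total | Power |
|---|---|---|---|
| One-sided 0.05 | 51 | 102 | 0.806 |
| Two-sided 0.05 | 64 | 128 | 0.801 |

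The plan's 102 is reproduced exactly, but only as a one-sided test. No margin enters the calculation.

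The number alone does not settle the framework. A noninferiority test with a margin of 0.5 SD and a true difference of zero has the same arithmetic. The text settles it, because 0.5 is presented as the intervention's effect on well-being and not as a tolerable loss.

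**2. What would a two-sided superiority statement need?**

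Inputs: 6 clusters, so k = 3 per arm; ICC ρ = 0.01; dropout 20%. The fixed-cluster formula, with n the individually randomised number per arm, is m = n(1 − ρ) / (k − nρ).

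- m = 64 × 0.99 / (3 − 0.64) = 63.36 / 2.36 = 26.8, rounded up to 27 per cluster.
- 27 × 6 = 162 in total.
- 162 / 0.8 = 202.5, rounded up to 203.

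This is below the planned 292. The plan's own step from 102 to 244 does not follow from this formula. That is a separate matter and is not relied on here.

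**3. How much room does a missing margin leave?**

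Assumptions: 292 × 0.8 ≈ 234 analysed (117 per arm, 39 per facility), ICC 0.01, and the T1 score alone in SD units.

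- Design effect = 1 + 38 × 0.01 = 1.38.
- SE = √(2 × 1.38 / 117) = 0.154 SD.
- Half-width with 1.96: 0.30 SD.
- Half-width with t on 4 df (6 clusters less 2 arms), 2.776: 0.43 SD.

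An estimate of exactly zero would therefore satisfy any later margin above about 0.30 SD or 0.43 SD, depending on the reference distribution. The benefit assumed in the plan is 0.5 SD.

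**4. Could the noninferiority label be kept?**

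The margins below are assumed, since the plan gives none. The other settings are SD 1, true difference 0, one-sided 0.025, 80% power, 3 clusters per arm, ICC 0.01, before dropout. The individually randomised number is n = 2(1.96 + 0.84)² / margin², followed by the formula in step 2.

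| Assumed margin | Individual n per arm | Total with 6 clusters |
|---|---|---|
| 0.5 SD | 63 | 162 |
| 0.4 SD | 99 | 294 |
| 0.3 SD | 175 | 834 |
| 0.25 SD | 252 | 3120 |
| 0.2 SD | 393 | not attainable (393 × 0.01 > 3) |

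With the plan's 122 evaluable per arm, the smallest margin with 80% power is about 0.42 SD.

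**The case against.** The strongest objection is that this is a mislabel and not a broken trial. A reader might infer from the missing margin that the trial can support no conclusion at all. The document does not bear that out: the planned GEE test of group × time can support a superiority conclusion whatever the design sentence says. This limit stands, and the point is confined to the label and to any noninferiority claim.

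A reader might also count the absence of a confidence-bound rule and of a per-protocol analysis. Both are details that a condensed article may leave to a fuller protocol or SAP, so they are not counted. The margin is different. The article sets out its sample-size derivation step by step, and a noninferiority sample size cannot be derived without a margin.

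Nor does the document say that a null result will be reported as noninferior. It speaks only of testing and concluding on intervention effects. The risk comes from what the wording leaves open and is not a stated intention.

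The half-width in step 3 is not that of the planned analysis. The plan names no degrees of freedom and intends multiple imputation. Its contrast is a change from T0 to T1, whose variance depends on a baseline correlation that is not given. That is why a range is shown, and the contradiction does not depend on it.

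**Conclusion.** The concern holds for the label. Two design statements say noninferiority, while the aim, the untreated comparator, the effect-based sample size and the difference test all say superiority, and no margin exists. The trial as planned cannot support a noninferiority conclusion, but it can support a superiority one. This should be corrected before results are read, because the framework decides how a null result is interpreted.

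The illustrative room for a post hoc margin is about 0.30 to 0.43 SD, under the assumptions in step 3. A second fact emerged from the check: 102 corresponds to an undisclosed one-sided 0.05 test, so relabelling is incomplete unless sidedness is stated.

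**What to change.** 1. In the Abstract and in Trial design, replace noninferiority with superiority. The registry record was not available for this review, so amend it only if it carries the same label.
2. State the primary hypothesis as a test of the group × time effect on WHO-5 from T0 to T1, matching Statistical methods, and state whether it is one-sided or two-sided.
3. State that a non-significant result will not be read as noninferiority.
4. In Sample size, disclose that 102 corresponds to a one-sided 0.05 test. If a two-sided test is declared, restate the base as 128, with about 162 after clustering and about 203 after 20% dropout.

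If the sponsor does intend noninferiority, the alternative is a justified margin with its own sample size and decision rule. Step 4 of the working shows that six clusters would make this impractical for margins of about 0.3 SD or less.

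The cost is a wording change in two places, a short hypothesis statement and a revised Sample size paragraph. By the fixed-cluster formula recruitment need not change. That formula makes no allowance for the few degrees of freedom left by six clusters, which is a separate question.

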### Study setting

The study will be conducted in facilities for older adults, including community centres and/or long-term care facilities for older adults in Hong Kong. Community centres for older adults provide various activities aiming to enable older adults to remain in the community and to lead a healthy, respectful, and dignified life [30]. Long-term care facilities for older adults provide residential care, meals, personal care, and nursing care for older adults who suffer from poor health or physical/mild mental disability [31].

### Participants

A convenience sampling approach will be employed. The eligibility criteria of the participants are below:

#### Eligibility criteria

Aged 60 years or above,Speak Cantonese and read traditional Chinese characters, andMentally capacitated is defined as having no diagnosed mental diseases leading to being mentally disabled and certified by a psychiatrist

### Interventions

#### Intervention group

The goal of the intervention is to enhance the ICT skills and promote the mental well-being of the older participants. A series of training sessions for a minimum of 23 h will be provided to the older adults. In the training sessions, the Digital Buddy will lead older adults to complete activity-based ICT tasks on their smartphones and answer questions they may have about smartphone usage. In the second half of the session, Digital Buddy will review the mental health contents assigned for each week and bring up group processing questions to encourage older adults to reflect on their attitudes about well-being and ageing. As shown in Table 1, the scope of the ICT skills includes foundational training for smartphone operation, usage of common social media platforms and safe web navigation for accessing information, while the scope of the mental health promotion includes stress relief, breathing and well-being, emotion regulations, and positive ageing. The whole intervention period will last for 6 months between 14 sessions. A systematic review of intergenerational interactions showed that the intervention programme length ranged from three months to three years but a six-month period is more commonly used for student-led programmes because it is more manageable for students within one school year [32].

**Table 1 Tab1:** ICT skills and mental health contents in the training sessions

Session	Duration	Training contents	
		ICT skills	Mental health
1	2 h	Introductory lesson	
2	2 h	1. Use of screen and operation buttons 2. Add phone contact 3. Review missed calls 4. Connect to internet	1. Review common symptoms in ageing adults 2. Practice a sensory relaxation technique 3. Engage in group processing questions
3	2 h	1. Use of camera functions 2. Use of a selfie camera 3. Create and organize photo album 4. Share photos on social media apps	1. Review tips to prevent anxiety 2. Practice the CABIN Relaxation Technique 3. Engage in group processing questions
4	2 h	1. Operate timer 2. Use of calculator 3. Use of voice-activated keyboard 4. Learn new functions of the LeaveHomeSafe App	1. Practice a 5-min guided mediation 2. Engage in group processing questions
5	1.5 h	1. Operate WhatsApp 2. Type and voice message 3. Share photo 4. Forward/delete message	1. Practice light stretching 2. Engage in group processing question
6	1.5 h	1. Register account 2. Compose an email 3. File attachment 4. Junk box	1. Practice pain relief massage 2. Engage in group processing question
7	1.5 h	1. The search function on YouTube 2. Like and favourite function 3. Create playlist	1. Practice abdominal breathing 2. Engage in group processing question
8	1.5 h	1. Create Zoom account 2. On and off for microphone and video camera 3. Write messages in a chat room	1. Practice hand-eye coordination exercise 2. Engage in group processing question
9	1.5 h	1. Download and operate HA GO app 2. Register an account 3. Book an appointment	1. Practice light cardio exercise 2. Engage in group processing question
10	1.5 h	1. Functions of the HealthCap app 2. Introduction to e123.hk	1. Practice breathing exercise 2. Engage in group processing question
11	1.5 h	1. Introduction to elderly.gov.hk 2. Introduction to elderlyinfo.swd.gov.hk	1. Practice a guided cognitive exercise 2. Engage in group processing question
12	1.5 h	1. Set and reset the password on the smartphone 2. Strategies to use the web safely	1. Practice posture-improving exercise 2. Engage in group processing question
13	1.5 h	1. Use of Samsung Health app 2. Practice light stretching exercises	1. Practice upper body stretching exercise 2. Engage in group processing question
14	1.5 h	Conclusion remarks	
Total	23 h		

The intervention will match up the older adults with the young adults (i.e. the Digital Buddy) in a ratio of 1 (young adults) to 10 (older adults). The study will recruit Digital Buddy if they are aged between 18 and 29 years and studying a full-time programme in a tertiary institution. The Digital Buddy will provide the training in a flexible group size, at a flexible place, and at a flexible time aiming to accommodate the availability of both older and young adults. A train-the-trainer programme will be provided by the research team to the young adult participants. The young adult participants will be qualified to become Digital Buddies in this programme after they have completed a 2-h train-the-trainer programme. The contents of the train-the-trainer cover the activities used to promote ICT skills and mental health promotion knowledge, as well as the essential communication skills with older adults.

The training materials are uploaded to a newly developed web-based platform (www.twcdigitalbuddy.hk), as shown in Fig. 1. This web-based platform contains all the educational materials in Chinese related to ICT skills and mental promotion in various forms (e.g. video-based mini-lectures, micro-movies, and video-guided demonstrations). The educational materials are either newly produced by the team or already available on the web, yet they are all reviewed and content-validated by an expert panel. After equipping the older participants with the ICT skills so that they can independently exercise these skills to communicate with the Digital Buddy, the Digital Buddy will deliver the training sessions or necessary coaching in person with the option to communicate on e-platforms (e.g. WhatsApp, Zoom). Both the older participants and the Digital Buddy will access the app-based training materials, attend coaching sessions, and communicate using smartphones over the course of the six months programme.

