### Statistical methods

Demographic and outcome data at baseline will be described either as means with standard deviation or as frequencies with percentages based on the level of measurement. Five generalized estimating equations (GEE) will be used to separately test the five outcomes. To test the hypotheses, the dependent variables will be mental well-being, depressive symptoms, health-related quality of life, self-efficacy, and social support across the two time points. The independent variables of the four hypotheses will be the same: group (i.e. intervention and control groups), time (i.e. T0 and T1), and group × time. The interpretation of the results will be based on intention-to-treat analysis [47]. We will primarily interpret the results using models without adjusting for possible co-variates because this will be an RCT without other known or anticipated important prognostic variables [48]. The level of significance will be set at 0.05. To manage missing data caused by unavoidable reasons (e.g. drop-out), the missing data will be replaced by multiple imputations following Jakobsen’s algorithm [49]. We will adopt an intention-to-treat analysis to conclude the intervention effects [47].

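### The sample size allows for one facility ICC in both arms and the GEE names no clustering unit, although Digital Buddies add a grouping level in the intervention arm only: a modest loss of precision

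*Protocol article*

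**What the plan says.** **Intervention group.** Older adults are matched with young adults "in a ratio of 1 (young adults) to 10 (older adults"). The Buddy leads the sessions, and Table 1 lists group processing questions in sessions 2 to 13 of 14. Group size, place and time are flexible.

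**Control group and Participant timeline.** Controls receive usual care without support from the research team. Their waitlist intervention starts in week 26, after the week 25 assessment (T1).

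**Assignment of interventions.** The facility is the unit of randomisation, and three clusters receive the intervention.

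**Sample size.** "We set the level of significance at 0.05, the power at 0.8, and the allocation ratio between the two groups at 1:1". The effect size "of the study of the intervention on the primary outcome (i.e. well-being) was 0.5", and "A sample size of 102 participants is needed". The adjustment is described as one "for cluster RCT with fixed and equal-sized number clusters". Then: "assuming that the intra-cluster correlation coefficient (ICC) is 0.01, the estimated total sample size is 244 (i.e. 122 per arm"). No value is given by arm or by Buddy.

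**Statistical methods.** The independent variables in each GEE are "group (i.e. intervention and control groups), time (i.e. T0 and T1), and group × time". Neither facility nor Buddy is named as the unit within which observations are correlated.

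**The concern.** With 122 to 146 participants in the intervention arm and 10 per Buddy, there are about 12 to 15 Buddy groups. Their members share one leader and repeated group discussion for six months. The Discussion expects most Buddies to be first-year students with little experience of volunteering with older adults, so differences between Buddies are plausible. Participants who share a Buddy may therefore have correlated outcomes at T1.

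An ICC that applies equally to controls, who have no Buddy, contains no Buddy component. Baseline is assessed before randomisation, so a Buddy effect can appear only at T1. It then falls on the group × time term that tests the intervention. Stable facility differences, by contrast, partly cancel in that term.

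Two things are at stake: how far the stated power holds, and, if clustering were ignored in the GEE, the false-positive rate.

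**Working it through.** **Inputs from the protocol.** d = 0.5, alpha 0.05, power 0.80, six facilities (three per arm), facility ICC 0.01, 122 per arm, 10 participants per Buddy. **Assumed, not in the document:** Buddy ICC (ρB) of 0.02, 0.05 or 0.10, meaning the extra correlation between participants who share a Buddy.

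**1. The plan's own figures.**
- A two-sample t-test with d = 0.5 and 80% power needs 51 per arm (102) one-sided or 64 per arm (128) two-sided. The printed 102 is the one-sided result; sidedness is not stated.
- With k clusters per arm, setting k·m = n[1 + (m − 1)ρ] gives m = n(1 − ρ)/(k − nρ).
- One-sided, n = 51 and k = 3: m = 50.49/2.49 = 20.28, so 21 × 3 = 63 per arm, total 126.
- Two-sided, n = 64 and k = 3: m = 63.36/2.36 = 26.85, so 27 × 3 = 81 per arm, total 162.
- The printed 122 per arm appears only with n = 102 and k = 6: m = 100.98/4.98 = 20.28, and 6 × 20.28 = 121.7. That enters the trial totals as if they were per-arm values.

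The 244 is therefore not reproduced with three clusters per arm. It is taken as given below because it is the printed sample.

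**2. Design effects at 122 per arm.** Facility size m = 122/3 = 40.67.
- Control: 1 + 39.67 × 0.01 = 1.397.
- Intervention: 1.397 + 9ρB = 1.577, 1.847 and 2.297.

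**3. Power.** SE = √[(DE_control + DE_intervention)/122] and ncp = 0.5/SE. The reference is either the noncentral t on 6 − 2 = 4 df or the normal.

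| ρB | DE, intervention | SE | Two-sided, 4 df | One-sided, 4 df | Two-sided, normal | One-sided, normal |
|---|---|---|---|---|---|---|
| 0 | 1.40 | 0.151 | 69.9% | 85.3% | 91.1% | 95.1% |
| 0.02 | 1.58 | 0.156 | 67.3% | 83.4% | 89.3% | 94.0% |
| 0.05 | 1.85 | 0.163 | 63.7% | 80.6% | 86.6% | 92.2% |
| 0.10 | 2.30 | 0.174 | 58.4% | 76.1% | 82.0% | 89.0% |

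Going from the normal to 4 df costs 91.1 − 69.9 = 21.2 points two-sided before any Buddy term. The Buddy term then costs 2.6, 6.2 or 11.5 points on 4 df, or 1.8, 4.5 or 9.1 points on the normal.

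If the Buddy variance is instead added on top of the control-arm variance (extra term 10ρB/(1 − ρB)), two-sided normal power is 89.1%, 85.8% and 79.8%.

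**4. At the 126 the inputs support.** One-sided normal power is 82.0% without a Buddy term and 79.6%, 76.0% and 70.5% with it. The larger printed sample is what absorbs the loss.

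**5. Error rate if participants were treated as independent.** For a simple T1 comparison, the true two-sided error is 2[1 − Φ(1.96/√D)], where D is the mean of the two design effects.
- Facilities only: D = 1.397, error 9.7%.
- ρB = 0.02, 0.05, 0.10: D = 1.487, 1.622, 1.847; error 10.8%, 12.4%, 14.9%.

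**The case against.** **The effect is small and rests on an assumed figure.** This stands. The document gives no Buddy ICC. Spread over about 41 people per facility, the three values equal an intervention-arm facility ICC of 0.01 + 9ρB/39.67, about 0.015, 0.021 and 0.033, and the 0.01 is itself an assumption. Fixed session content, shared validated materials and a staff member at the training sessions may all limit differences between Buddies. Group size is flexible, so 10 is nominal.

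**A reader might infer that Buddy clustering takes the trial below 80% power.** The figures do not support that in general. Two-sided on 4 df, power is already 70% with no Buddy effect, because there are only six facilities. On the other three bases in the table it drops below 80% only at a Buddy ICC of 0.10 with one-sided 4 df. Adding the Buddy variance on top brings the two-sided normal figure to just under 80%, again only at 0.10.

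**A reader might also infer that the GEE ignores clustering.** The article does not say so. The clustering unit and any small-sample correction may stand in an analysis plan that is not shown, so the inflated error rates are conditional. The sample-size part is firmer, because its ICC and cluster count are printed.

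**Facility-level inference would cover Buddy groups anyway.** This is right for the error rate if each Buddy works within one facility. That is plausible but not stated, and flexible places and online contact leave it open. It would not restore the precision lost.

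**Conclusion.** The point holds as a modest one. The stated power leaves out a grouping level that the design creates in one arm, and the described models do not name the randomised facility as the unit of correlation. For Buddy ICCs of 0.02 to 0.10 the loss at the printed 244 is about 3 to 12 points of two-sided power on 4 df, or 2 to 9 points by normal approximation. The small number of facilities costs more than this, and so weighs more.

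These sizes rest on the assumed Buddy ICC, groups of 10, equal facilities, Buddies working within one facility, and the printed 244, which the plan's inputs do not yield. The more serious consequence, a false-positive rate of about 10% from facilities alone and 11% to 15% with Buddies, arises only if the GEE treats participants as independent. The document neither states nor excludes that.

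**What to change.** - **Statistical methods:** make the facility the independent unit in every GEE, with a small-sample correction and a t reference on about 4 df. State whether each Buddy works within one facility; if so, this also covers the Buddy groups.
- **Sample size:** state whether the test is one- or two-sided. Restate the power with a Buddy term in the intervention arm, 1 + (m − 1) × facility ICC + 9 × Buddy ICC, over a range such as 0.02 to 0.10. Present it as a sensitivity range without enrolling more. The derivation of 244 should be reconciled at the same time.
- **Data collection:** record each participant's Buddy so that the Buddy ICC can be reported. With flexible groups, places and times, this may be hard to reconstruct later.

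The cost is protocol wording, one identifier per participant, a less favourable stated power and wider intervals. No extra participants are needed.
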